### Design

A phase I formative research [43] will be performed in four PHC centres of the Basque Health Service – OSAKIDETZA. In a first descriptive stage, a strategic needs assessment will be carried out along with the prioritisation of the areas of preventive practice to be optimised and selection of the aims of the programmes. In a second, creative stage, specific objectives of intervention will be identified based on theoretical models of behaviour change and collaborative design of specific intervention actions for addressing and managing multiple risk behaviours will be undertaken.

Within the formative research, a quasi-experimental pre-post evaluation study will be performed to compare the changes in indicators related to health promotion practice in the four PCCs assigned to the aforementioned formative research process (Intervention Group) and those of other four centres, matched in structural and population characteristics (Control group) [46]. Additionally, Nominal Groups will be performed with professionals belonging to intervention centres, in order to identify the successes, strengths, weaknesses and shortcomings of the process, as well as experiences concerning its usefulness, and difficulties and barriers with respect to the cooperation between researchers and clinicians and between professions within the centres.

The project was approved by the Institutional Primary Care Research Committee of the Basque Health Service/Osakidetza, on 12^th ^April 2007, by the Basque Country Clinical Research Ethics Committee (Ref: 06/2008), and evaluated and approved for funding by the Basque Government Department of Health (Ref: 2007111009).

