#### Recruitment process of the Health Centres and PHC professionals

The identification of the eligible centres was performed via the Medical Directors of the seven divisions of primary care services, under which the PHC of the Basque Health Service – OSAKIDETZA is organised. Four of them accepted to collaborate and they each selected two primary care centres with similar structural and population characteristics. Project presentation sessions were given to the professionals of the selected centres, in which members of the research group explained the scientific and methodological details of the project, and the work plan. Then, each of the professionals were invited to collaborate through the presentation of an informed consent form. The majority of the professionals of each profession agreed to collaborate in eight of the centres; four of them being assigned for convenience to the formative research process, and the other four forming the reference or Control Group. Finally, 130 professionals (82 in the Intervention Group and 48 in the Control Group), collaborated in the project: 46 family doctors (29 in the Intervention and 17 in the Control), 45 nurses (26 in the Intervention and 19 in the Control), 27 administrative officers (18 in the Intervention and 9 in the Control), 10 paediatricians (8 in the Intervention and 2 in the Control), 3 midwives (2 in the Intervention and 1 in the Control group) and 1 social worker (Fig 1).

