### Analysis

In order to evaluate the changes associated with the formative process, quantitative comparisons will be performed between the professionals assigned to the Intervention Group and those from the Control Group, on an intention to treat basis. The means of continuous variables will be compared using the Student's t test and the proportions using the Chi-square test. The differences between the two groups will be estimated and the 95% confidence interval calculated. The comparisons will be adjusted for potential confounding factors by stratified analysis. Finally, multivariate statistical models, linear for continuous variables and logistic for proportions, will be constructed in order to simultaneously account for possible confounding effects, following a "forward strategy" guided by the aforementioned stratified analysis. The sample size of the present formative research study (130 health professionals, 30% in the control group) will provide a greater than 80% power to detect as significant (alpha = 0.05) a difference of at least 20% (improvements of 5% and 25% in the control and intervention groups, respectively) in the proportion of professionals that report to ask and advice about healthy lifestyles to the mayority of their patients.

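### Confounders in a convenience-assigned comparison are picked by forward selection from the outcome data, which can drop real confounders and gives intervals that ignore the selection

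*Protocol article*

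**What the plan says.** The Recruitment section reports that eight centres agreed to take part, "four of them being assigned for convenience to the formative research process, and the other four forming the reference or Control Group". The Design section describes the evaluation in these terms: "a quasi-experimental pre-post evaluation study will be performed to compare the changes in indicators related to health promotion practice". It says the control centres are "matched in structural and population characteristics (Control group".

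The Analysis section then sets out three steps.

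- Unadjusted comparison: "The means of continuous variables will be compared using the Student's t test and the proportions using the Chi-square test".
- Stratification: "The comparisons will be adjusted for potential confounding factors by stratified analysis".
- Multivariable models, "linear for continuous variables and logistic for proportions, will be constructed in order to simultaneously account for possible confounding effects", built "following a 'forward strategy' guided by the aforementioned stratified analysis".

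The section gives no entry criterion for the forward step and does not say that any covariate is kept in regardless of the data.

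**The concern.** Without randomisation, the causal reading of the group difference rests partly on adjustment at the level of the professional. The article fixes how that adjustment is chosen: the stratified results guide the forward step, and both use the outcome data that also supply the effect estimate. Two problems follow.

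- A confounder of moderate strength may fail to enter with about 130 people. The adjusted estimate then stays partly biased towards the unadjusted one.
- The model's standard error treats the selected model as fixed in advance, so the 95% interval tends to be too narrow.

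A third problem is practical. With the entry rule open, the same data can yield several adjusted answers.

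Profession shows why the choice should not be left to an entry test. The powered outcome is whether professionals ask and advise patients about lifestyle, and administrative officers are counted together with clinicians. The professional mix also differs between groups, for example "10 paediatricians (8 in the Intervention and 2 in the Control".

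**Working it through.** **The plan's own figure.** The only number in the Analysis section is the power statement. With n = 39 and 91 (30% of 130 in control), rates 0.05 and 0.25, and two-sided alpha 0.05:

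- Pooled rate = (39×0.05 + 91×0.25)/130 = 0.19.
- Null SE = √(0.19×0.81×(1/39+1/91)) = 0.0751.
- Alternative SE = √(0.05×0.95/39 + 0.25×0.75/91) = 0.0573.
- Power = Φ((0.20 − 1.96×0.0751)/0.0573) = 82.2%.

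The statement of more than 80% reproduces and is not disputed here.

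**Balance of profession (Recruitment section).** Nurses are 26/82 = 31.7% against 19/48 = 39.6%. Paediatricians are 8/82 = 9.8% against 2/48 = 4.2%. Family doctors are 29/82 = 35.4% against 17/48 = 35.4%. These shares are approximate, because the itemised professions add to 46+45+27+10+3+1 = 132, not 130.

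**Illustration, linear model.** From the article: n = 82 and 48. Assumed: true effect 0, residual SD 1, no clustering, and K = 6 independent confounders. Each differs by d SD between groups and has coefficient b. There were 1,500 to 2,000 runs per setting.

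The bias left by omitting m confounders is m×d×b. Omitting all six gives 6×0.3×0.15 = 0.27, and the simulation gave 0.268.

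| d, b | Model | Bias | Mean SE / true SD | Type I error |
|---|---|---|---|---|
| 0.3, 0.15 | unadjusted | 0.27 | 0.193 / 0.192 | 28% |
| 0.3, 0.15 | forward, p<0.05 | 0.11 | 0.188 / 0.211 | 11% |
| 0.3, 0.15 | forward, >10% change | 0.01 | 0.196 / 0.211 | 6% |
| 0.3, 0.15 | all six fixed | 0.00 | 0.197 / 0.196 | 4.4% |
| 0.5, 0.15 | forward, p<0.05 | 0.18 | 0.196 / 0.242 | 22% |
| 0.5, 0.15 | forward, >10% change | 0.01 | 0.213 / 0.231 | 9% |
| 0.5, 0.15 | all six fixed | 0.00 | 0.216 / 0.216 | 4.8% |

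The following results come from the same table and from further runs.

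- Bias removed by p<0.05 entry: (0.268−0.111)/0.268 = 59% at d = 0.3, and (0.453−0.181)/0.453 = 60% at d = 0.5.
- SE shortfall under p<0.05 entry: 1 − 0.188/0.211 = 11%, and 1 − 0.196/0.242 = 19%.
- SE shortfall under the change-in-estimate rule: 1 − 0.196/0.211 = 7%, and 1 − 0.213/0.231 = 8%. A further run at d = 0.3 gave 1 − 0.196/0.206 = 5%.
- Repeated runs of the first setting with p<0.05 entry gave errors between 11% and 14%. The fixed model gave 4.4% to 7.4%.
- With d = 0.15, p<0.05 entry gave bias 0.056 and error 7.3%. With no imbalance, or with no confounder effect, the error was about 5%.

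**Illustration, logistic model.** The powered outcome is a proportion. If 5% and 25% are its rates, the events number 0.05×48 = 2.4 and 0.25×82 = 20.5, about 23 in all. Assumed: true null, about 18% events, and log-odds 0.4 per SD. With significance entry, each real confounder entered in only 36 to 39% of runs.

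| Confounders | Unadjusted bias (log-odds) | Forward bias | Forward error |
|---|---|---|---|
| three, d = 0.3 | 0.34 | 0.17 | 5.6% |
| three, d = 0.5 | 0.57 | 0.25 | 8.5% |
| six, d = 0.3 | 0.64 | 0.31 | 10.8% |

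The fixed model left a bias of about 0, with errors of 4.1 to 4.4%.

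**Testing the remedy (linear, d = 0.3, b = 0.15).** Fixing only two of the six confounders leaves 4×0.3×0.15 = 0.18. Simulation gave 0.177 and 0.185, with errors of 14% and 16%, which is worse than forward selection. Forcing two in and still considering the other four gave bias 0.076 and error 8%. Fixing all six gave no bias and about 4% error.

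**The case against.** A reader might infer that adjustment is the only protection against confounding here. The documents do not support that. Each of four divisions selected two centres of similar structure and population, all centres had to meet the same interest and cooperation criteria, and the pre-post comparison of changes reduces the influence of stable baseline differences. This stands. It does not dispose of the point, because matching centres does not by itself balance professional mix or baseline practice among individuals.

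A reader might also infer that the plan will certainly leave residual confounding. That does not follow either. No p-value is stated, and guidance by stratified analysis is at least as compatible with comparing crude and adjusted estimates. Under that rule the bias nearly disappears, and only the modestly narrow intervals remain.

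The confounding scenario is also adverse, with six independent confounders all imbalanced in the same direction. Weaker imbalance gives little inflation. Small profession categories can be merged, so sparse strata are not an inevitable consequence of the plan.

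A condensed article may fairly leave the list of covariates to a fuller plan, and its absence is not the point here. The forward strategy is a method that the article itself fixes.

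A short fixed set is no automatic improvement, as the two-covariate result shows. That objection stands and shapes the fix.

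**Conclusion.** The point holds in a conditional form. The article commits to choosing confounders from the outcome data, in a comparison allocated by convenience. This can drop real confounders, materially so if entry is by significance. Under both entry rules examined, the interval takes no account of the selection.

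With six assumed confounders 0.3 to 0.5 SD apart (coefficient 0.15), significance entry gives a type I error of roughly 11 to 22% and standard errors 11 to 19% too small. Change-in-estimate entry gives 6 to 9% and 5 to 8%. With little or no imbalance the error is close to 5%.

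These figures rest on an assumed number, strength and imbalance of confounders, an assumed entry rule and no clustering. They are illustrations and not properties of the plan. Fixing the adjustment set in advance does not cure unmeasured confounding or the limit of eight centres. The change is worth making because it is cheap and uses data already collected.

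**What to change.** Replace the forward strategy for the primary adjusted analyses with a set named on subject-matter grounds before post-programme data are seen. Force it into every such model regardless of significance. The set should contain at least:

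- the professional's pre-programme value of the outcome;
- profession in three groups: doctors including paediatricians, nurses and midwives, administrative and other;
- any other measured factor judged in advance to be a confounder.

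Do not reduce the set to the first two items if other confounders are expected. Keep the stratified analyses as descriptive, and label any forward-selected model as a sensitivity analysis.

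The cost is wording only. The questionnaire is already given before and after the programme, and profession is recorded. The core set takes about three degrees of freedom (one for baseline, two for profession). Logistic models may meet sparse-data problems if control events are as few as two or three, and a penalised fit would handle that.

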### Participants

#### Eligibility criteria

The particular focus of this study, which aims to introduce a process of change in health promotion practice in PHC under a framework of participative research with health professionals, community partners and researchers, determines the two characteristics that define the participants: (1) the intervention unit is the PCC; and (2) the centre must be especially interested in health promotion. The creative work to be undertaken requires that the professionals and health centres be positively motivated with respect to changing risk behaviours of their patients and the integration of health promotion in daily practice. That is why the following factors were considered in order to identify the centres that were eligible: (1) previous history of participation or evaluation of programmes for health promotion in the last 10 years, (2) previous initiatives of preventive practice optimisation and the promotion of healthy lifestyles, (3) existence of programmes, resources, services or initiatives for health promotion in the community or geographical area of reference, (4) positive attitude to working together and cooperation between the professionals of the centre, (5) centres in which it would be possible to make some kinds of changes in the organisation of services, once the potential innovative strategies for approaching multiple risk behaviours have been determined. The commitment of cooperation by a majority plus one of all the professionals of the centre for each of the professions (administrative officers, nurses, family doctors, paediatricians and others) was required to participate in the project.

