**Figure 1 F1:**
[figure not shown]
**Operational organization of the formative process "Prescribe Vida Saludable" in the intervention centres**. **Note**: HC, Health Centre; GP, General Practitioner; Nur, Nurse; Ped, Paediatrician; AS, Administrative Staff; Epi, Epidemiologist; Soc, Sociologist; Psi, Psychologist. Participation in Control health centres, Beraun HC: GP (5), Nur (4), Ped (1), AS (2), Social worker (1); Markina HC: GP (5), Nur (5), AS (3); Berango HC: GP (2), Nur (2), Ped (1), AS (1); and Zurbaran HC: GP (5), Nur (8), AS (3).

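### The stated power of over 80% at alpha 0.05 treats 130 professionals as independent; with whole centres assigned 4 versus 4, that power and that alpha cannot both hold once colleagues in a centre are correlated

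*Protocol article*

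**What the plan says.** Three statements in the protocol article bear on this point.

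- **Unit of intervention.** Under Eligibility criteria, "the intervention unit is the PCC", that is, the primary care centre. The Formative Research section has sessions run centre by centre, with one prioritised goal per centre.
- **Assignment.** Under the recruitment of health centres and professionals, eight centres entered, "four of them being assigned for convenience to the formative research process, and the other four forming the reference or Control Group". In all, "130 professionals (82 in the Intervention Group and 48 in the Control Group), collaborated in the project".
- **Power and tests.** The Analysis section bases its power on "130 health professionals, 30% in the control group", assumes "improvements of 5% and 25% in the control and intervention groups, respectively", and says the sample "will provide a greater than 80% power to detect as significant (alpha = 0.05) a difference of at least 20" percentage points. The tests it names are Student's t for means and chi-square for proportions, followed by stratified analysis and linear or logistic models to deal with confounding. The power statement mentions neither the number of centres nor any correlation within them.

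**The concern.** Professionals in one centre share sessions, a common goal, pilots, workload and organisation, so their answers about their own practice are unlikely to be independent. The between-group comparison rests on eight centres, but the power sentence counts 130 separate people.

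What is at stake is the pair of promises in one sentence: over 80% power *and* a 5% significance level. If the analysis ignores centre, the 5% level is lost and a difference between centres can pass for an effect of the programme. If the analysis respects centre, the 5% level is kept and the power is lower than stated. The sentence is therefore wrong whichever analysis the full plan contains.

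**Working it through.** **Inputs from the article.** 5% versus 25%; alpha 0.05 (taken as two-sided); 130 professionals, with 30% control in the Analysis section (39/91) and 48/82 in the recruitment section; 4 + 4 centres; control centre sizes 13, 13, 6 and 16 from the note to Figure 1 (sum 48).

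**Assumptions, because the article does not give them.** ICC from 0.01 to 0.10; intervention centres of about equal size, 82/4 = 20.5.

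**Step 1: reproduce the stated figure.** For independent people, with a pooled two-proportion test, power = Φ[(0.20 − 1.96·SE0)/SE1], where SE0 is the standard error under no difference and SE1 the one under 5% versus 25%.

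- 39/91: pooled proportion 0.190, SE0 = 0.0751, SE1 = 0.0573; (0.20 − 0.1472)/0.0573 = 0.92, power 82%.
- 48/82: pooled proportion (2.4 + 20.5)/130 = 0.176, SE0 = 0.0692, SE1 = 0.0572; (0.20 − 0.1357)/0.0572 = 1.12, power 87%.

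Both exceed 80%, so the figure is reproduced as an independence calculation. At 30/70 the formula needs 38 controls, about 38/0.30 = 127 people in all. The 130 leave almost no room for a design effect.

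**Step 2: a centre-level test.** The design effect is 1 + (m − 1)·ICC. For the intervention group m = 20.5. For the control group the size-weighted m = (169 + 169 + 36 + 256)/48 = 630/48 = 13.1. Then SE = √(0.25·0.75·DE_I/82 + 0.05·0.95·DE_C/48), and power comes from a noncentral t with 8 − 2 = 6 degrees of freedom (critical value 2.447).

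At ICC 0.05: DE_I = 1 + 19.5·0.05 = 1.975; DE_C = 1 + 12.1·0.05 = 1.606; SE = √(0.00452 + 0.00159) = 0.0781; noncentrality 0.20/0.0781 = 2.56; power 57%. The effective sample is 82/1.975 + 48/1.606 = 41.5 + 29.9 = 71. Putting 33% in place of 25% gives 80% power, so the detectable difference is about 28 points.

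**Step 3: the test the article names.** Simulation with beta-binomial centre effects (30,000 runs per setting, control centres as in Figure 1, intervention centres 20/20/21/21). Power is for 5% versus 25%; type I error is with both groups at 15%.

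| Assumed ICC | Individual chi-square: power | Individual chi-square: type I error | Centre-level t, 6 df, formula: power | Centre-level t, 6 df, simulated: power | Design effect, pooled normal test: power |
|---|---|---|---|---|---|
| 0.01 | 88% | 6.9% | 77% | 75% | 81% |
| 0.02 | 86% | 8.5% | 71% | 71% | 76% |
| 0.05 | 83% | 13.6% | 57% | 59% | 63% |
| 0.10 | 80% | 21.3% | 43% | 46% | 47% |

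The simulated centre-level t test held its type I error at 4.5-5.3% over this range.

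**The case against.** Several objections have weight.

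- **The arithmetic is right.** From its own inputs the sentence gives 82% or 87%. This stands. The fault is the unstated assumption of independence, not a slip in calculation.
- **The planned test keeps its power.** A reader might infer that the study as planned has only 43-77% power, so that a null result could easily hide a 20-point effect. The article does not support that. It names an individual-level chi-square test, which keeps roughly the stated power. The risk under that test is a false positive.
- **Not every small ICC breaks the claim.** A reader might also infer that any clustering takes power below 80%. With a design effect and a pooled normal test, power at ICC 0.01 is still about 81%. In the formula of step 2, a normal reference in place of t on 6 df would give about 90% at ICC 0.01 and 85% at 0.02. At these low values much of the loss comes from having 6 degrees of freedom. By ICC 0.05 every cluster-aware version tried is below 80%.
- **The figures are conditional.** The article gives no ICC, and the intervention centre sizes belong to a figure not shown. The calculation also compares unpaired, single-time proportions, whereas the Design section describes a pre-post comparison of matched centres. Baseline adjustment or pairing would change both the variance and the degrees of freedom, in a net direction the article does not settle.
- **It is phase I work and recruitment is complete.** The figure no longer drives enrolment, and no go or no-go rule depends on it. This lowers the severity. It does not rescue a formal power claim made for the effect on self-reported practice, the primary outcome.

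**Conclusion.** The point holds in this form: over 80% power at alpha 0.05 is an independence figure, and the design assigns centres. With within-centre correlation, either the type I error rises (about 7% to 21% for the individual chi-square over ICC 0.01 to 0.10) or the power of a valid centre-level test falls (about 77% to 43% over the same range).

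That the figure ignores clustering follows from the article alone. The sizes depend on the assumed ICC range, near-equal intervention centres, an unpaired comparison and, for the lower powers, a 6-df centre-level test that the article does not name. The severity is should-fix: the claim needs correcting, but nothing in recruitment hangs on it.

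**What to change.** Change the analysis and the power sentence together. Quoting a lower power while leaving the individual-level tests in place would describe a test that is not run.

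1. Account for centre in the between-group comparison, with a small-sample correction for eight centres: for example a t test on centre-level summaries, or a mixed model with corrected degrees of freedom.
2. Restate the power for that analysis, using the actual split of 82/48 (48/130 = 37% control, not 30%), the number of centres, the assumed ICC range, the resulting power and the detectable difference. For example: *With 82 and 48 professionals in four and four centres, a two-sided 5% centre-level t test (6 df) has about 57% power for 5% versus 25% at an assumed ICC of 0.05 (77% at 0.01, 43% at 0.10); at ICC 0.05 the difference detectable with 80% power is about 28 points.*
3. Describe the comparison as exploratory or estimation-focused, which suits a phase I modelling study.

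The sample should not be enlarged for this. The cost is a few sentences and a modified model. The stated power becomes less favourable and the confidence intervals widen.
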